### Study participants

Study participants will comprise two groups of critically ill patients with AKI on CRRT.

### Inclusion criteria

Patients are eligible for inclusion if they give consent, develop AKI, need CRRT, weigh between 45 and 150 kg, and are more than or equal to 18-years-old.

### Exclusion criteria

These include: a) admission diagnosis of major trauma, b) need for therapeutic anticoagulation, c) contraindication to heparin-allergy or HIT, d) pregnancy, e) life-support limitation, f) uncontrolled hypertension (blood pressure >180/110) for at least 12 hours, g) cerebral hemorrhage or acute gastrointestinal bleeding, h) severe thrombocytopenia (platelet count <50 × 109/l), i) International Normalized Ratio (INR) or activated partial thromboplastin time (APTT) more than or equal to two times the upper limit of normal, j) chronic renal failure or acute-on-chronic renal failure, and k) initial evaluation after more than 24 hours have elapsed from commencement of CRRT.

### Randomization

All patients who fulfil the inclusion criteria and who give consent for participation will be randomized. The randomization sequence was generated in block sizes of four by the hospital’s pharmacy at OUH, using a web-based randomization system. This allocation sequence is being implemented through use of sequentially numbered, opaque, sealed envelopes. Each center will screen subjects to achieve the enrolment targets demonstrated in Figure 1. In the event of failure to meet target population, the study will be expanded to other sites. Allocation concealment will be ensured as the randomization code will not be revealed until the patient has been recruited into the trial.

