## Methods/Design

### Trial design

This is a multicenter randomized controlled trial conducted at three ICUs across Denmark to assess whether a dose of 1 mg/kg enoxaparin versus standard dose of 40 mg enoxaparin will improve thromboprophylaxis in AKI patients on CRRT, without increasing the risk of bleeding. We will randomly assign eligible critically ill adults with AKI into a treatment arm (1 mg/kg enoxaparin sc QD) or a control arm (40 mg enoxaparin sc QD) upon commencement of CRRT. The sample population will consist of 133 patients from ICUs at Odense University Hospital (OUH), Svendborg Hospital, and SVS Esbjerg Hospital. An interim analysis will be conducted after the first 67 patients have been included in each group. Enrolment began in March 2013 and will continue until March 2015. Patients will be followed until either: (1) a combination of VTE and renal recovery, (2) a combination of heparin - induced thrombocytopenia (HIT) and renal recovery, (3) ICU death or discharge, or (4) change from continuous to intermittent dialysis. Investigators will obtain consent for the collection of data on treatments and outcomes for participants who withdraw prematurely from the project. Many of the current investigators have participated in other trials and, as such, have a proven track record with respect to enrolment and follow-up of participants and collecting complete data sets. We will document the reasons for missing data, collect auxiliary variables that may predict outcome and/or determine which patients are more susceptible to dropout, and follow-up on all such patients until 24 hours after the last dose of enoxaparin.

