	Enoxaparin will be administered subcutaneously to the thigh or abdomen of the study patients from the day of inclusion, until the end of each participant’s study period.
Key inclusion and exclusion criteria	Inclusion criteria: patients are eligible if they give consent, develop acute kidney injury, need continuous renal replacement therapy, weigh 45 to 150 kg, and are ≥18 years.
	Exclusion criteria: these include a) admission diagnosis of major trauma, b) need for therapeutic anticoagulation, c) contraindication to heparin (allergy or heparin-induced thrombocytopenia), d) pregnancy, e) life-support limitation, f) uncontrolled hypertension (bp > 180/110) for at least 12 hours, g) cerebral hemorrhage/acute gastrointestinal bleed, h) severe thrombocytopenia (platelet count <50 × 109/l), i) International Normalized Ratio (INR) or activated partial thromboplastin time (APTT) ≥2 times the upper limit of normal, j) chronic renal failure or acute-on-chronic renal failure, and k) initial evaluation more than 24 hours after commencement of continuous renal replacement therapy.
Study type	Interventional allocation: randomized
	Intervention model: double arm
	Masking: double blind (subject, relatives, investigator, outcomes assessor)
	Primary purpose: prevention
Date of first enrolment	March 2013
Target sample size	266
Recruitment status	Recruiting
Primary outcome(s)	Venous thromboembolism
Key secondary outcomes	Catheter-related thrombus, anti-Xa activity, bleeding, heparin-induced thrombocytopenia, filter lifespan, length of stay, ventilator free days, and mortality. We will monitor neutrophil gelatinase-associated lipocalin levels and urine volume to determine whether they can be used as prognostic factors for renal recovery.

**Table 2 T2:** Protocol revision chronology

**Date**	**Protocol amendment**
Original version, 22.02.2011	Amendment Number 1:
	Primary reason for amendment:
	Changes in the methods sections - a decision to allow the pharmacy at OUH to generate randomization code was made.
Version 2, 18.05.2011	Amendment Number 2:
	Primary reason for amendment:
	At the request of GCP changes in the ethics section to elaborate on the procedure for obtaining consent.
Version 3, 18.07.2012	Amendment Number 3:
	Primary reason for amendment:
	The methods section was amended to include a description of the conduct of CRRT during the trial.
Version 4, 25.08.2012	Amendment Number 4:
	Primary reason for amendment:

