### Blinding

The medicine module of Critical Information System (CIS LIVE™; Daintel, Copenhagen, Denmark) used at all three hospitals allows for blinding. Patients, family members, clinicians, research personnel, radiologists, laboratory technicians, and the trial biostatistician will all be unaware of study-group assignments. They will remain blinded until the study database is locked at the end of the trial. Nurses who administer the drug will be the only party privy to the actual dose given to each patient as it is impossible to prepare an enoxaparin dose of 1 mg/kg beforehand. In the event of an emergency (major bleeding, need for major surgery), a participant’s allocated intervention may be revealed to the attending duty physician by the nurse providing care for that participant. The actual allocation will not be disclosed to the patient or study personnel, and there will be no disclosure of the code in any of the corresponding patient documents.

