### Sample size and statistical methods

We hypothesized that the optimal dose of enoxaparin would reduce the incidence of VTE in critically ill AKI patients requiring CRRT without causing an increase in bleeding. An additional hypothesis was that high urine output prior to the discontinuation of dialysis and low NGAL in dialysis-free intervals can predict renal recovery in these patients.

We estimated that with 133 patients in each group the study would have 80% power to show a 40% reduction in the relative risk of VTE with 1 mg/kg enoxaparin sc QD, assuming an incidence rate of 40% in the control group, at a two-sided alpha level of 0.05. An interim analysis (for both safety and efficacy) after approximately 50% of the patients have completed the study will be performed by an independent statistician blinded to the treatment allocation. These outcomes will be analyzed with stopping rules based on the Fleming-Harrington-O’Brien stopping boundary using *P* = 0.01, with adjustment for an overall type 1 error of 0.05, and with the final analysis conducted at *P* = 0.045 [21]. The statistician will report, in strict confidence, to the DMC (see Table 3). The DMC members will not be blinded to patient allocation. They may request other analyses (such as data from other comparable trials) prior to reaching a decision on the continuation of the trial. The DMC will report its recommendations in writing to the Trial Steering Committee. The study can also be terminated if the difference between groups is negligible and the statistician using ’conditional power’ calculation determines that continuation will be futile.

**Table 3 T3:** Organizational structure and responsibilities

**Title**	**Name(s)**	**Function(s)**
Principal investigator and Research Physician	[name], MB, BS; EDIC	Design and conduct of trial F.B.I., protocol preparation and revisions, preparation of Case Report Forms, managing Clinical Trials Office, publication of study reports,member of both committees, and organization of steering committee meetings.
Lead investigators	[name], MB, BS; EDIC Odense University Hospital	Maintain trial master file and resolve contractual issues at sites
	[name], Phd	
	Svendborg Hospital	
	[name] [name] SVS Esbjerg Hospital	Responsible for identification, recruitment, data collection, and completion of CRFs, along with follow-up of study patients and adherence to study protocol.
Steering committee	[name], MB ,BS; EDIC	Agreement of final protocol

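### One fixed, published block size of four would let up to a third of allocations be deduced if earlier doses leak from the bedside

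*Protocol article*

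**What the plan says.** On the list, the Randomization section states: "The randomization sequence was generated in block sizes of four". It was produced by the pharmacy of the lead hospital and is applied through numbered sealed envelopes. The section regards concealment as secured because the code stays hidden until a patient has been recruited. It does not say whether there is one list for the three centres or one list per centre.

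On who knows the arm, the Blinding section states: "Patients, family members, clinicians, research personnel, radiologists, laboratory technicians, and the trial biostatistician will all be unaware of study-group assignments". The exception is at the bedside: "Nurses who administer the drug will be the only party privy to the actual dose given to each patient". In an emergency, such as serious bleeding or a major operation, "a participant’s allocated intervention may be revealed to the attending duty physician by the nurse providing care for that participant". The section adds that study personnel are not to be told and that the code is kept out of patient documents.

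On who recruits, the Ethics section says that research physicians on the three ICUs obtain consent.

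**The concern.** Sealed envelopes and a hidden code stop a recruiter from reading the next allocation. They do not stop someone from working it out. With 1:1 blocks of one known size, each earlier allocation narrows what can follow, and the last place in every block is fixed.

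Earlier allocations are visible to some staff on the units where patients are recruited. Entry requires a weight of 45 to 150 kg, so the weight-based dose is 45 to 150 mg and never equals the control dose of 40 mg. A nurse who gives a dose according to allocation can read the arm from it.

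If a recruiter could anticipate the next arm, a patient thought likely to bleed might be enrolled or held back accordingly. The trial's hypothesis is less venous thromboembolism without more bleeding, so selection of that kind would bear directly on the safety comparison, and analysis cannot reliably repair it.

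**Working it through.** The article gives no figure for predictability, so there is none to reproduce. The shares below follow from the block size. The sample size only converts a share into a count.

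**Inputs**
- Block size 4, one size only (Randomization).
- Ratio 1:1, inferred from equal groups: "We estimated that with 133 patients in each group the study would have 80% power" (Sample size and statistical methods).
- Total 2 × 133 = 266, as in Table 1: "Target sample size 266".
- Three centres: "This is a multicenter randomized controlled trial conducted at three ICUs across Denmark" (Trial design).

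The 133 per group is consistent with its stated assumptions (40% against 24%, two-sided 0.05, 80% power). The pooled two-proportion formula without continuity correction gives 133, with power 80.2%.

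**1. Everything earlier in the block is known.** There are 6 equally likely orders of two A and two B.
- Places 1 and 2 are never certain.
- Place 3 is certain when the first two match, which happens in 2 of 6 orders: probability 1/3.
- Place 4 is always certain.
- Certain share = (0 + 0 + 1/3 + 1) / 4 = 1/3 = 33.3%. Applied to 266 patients: 266 / 3 = 88.7, about 89.

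Best-guess success by place is 1/2, 2/3, 2/3 and 1. The mean is (17/6) / 4 = 17/24 = 70.8%, against 50% with no knowledge.

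**2. Only some earlier allocations are known.** Suppose each is known independently with probability q (an assumption), and the start of the block is known.
- Place 3 is certain if both earlier allocations are known and match: q²/3.
- Place 4 is certain if both members of the matching pair among the first three are known: q².
- Certain share = (q²/3 + q²) / 4 = q²/3.

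| q | Certain share |
|---|---|
| 1 | 33.3% |
| 0.9 | 27% |
| 0.75 | 19% |
| 0.5 | 8.3% |
| 1/3 | 3.7% |
| 0 | 0% |

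The row q = 1/3 represents one list shared by three centres with equal recruitment, where staff learn only their own centre's doses.

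**3. What other block schemes would do.** All earlier allocations are taken as known. Fixed sizes were enumerated exactly. Varied sizes were simulated (400 sequences of 266, sizes equally likely). The person predicting knows the set of possible sizes but not the size of each block.

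| Scheme | Certain | Best guess right |
|---|---|---|
| Fixed 4 | 33.3% | 70.8% |
| Fixed 6 | 25% | 68.3% |
| Fixed 8 | 20% | 66.6% |
| Varied 2, 4, 6 | 4.0% | 70.2% |
| Varied 4, 6 | 5.5% | 69.3% |
| Varied 4, 6, 8 | 2.3% | 68.0% |

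Varied 4, 6 and 8 leaves about 0.023 × 266 = 6 certain allocations. Varying the size removes most of the certainty but little of the advantage in guessing. Including size 2 leaves best-guess success almost where it is now.

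**The case against.** The strongest reply is that the protocol keeps the two kinds of knowledge apart. Research physicians recruit and are stated to be blinded. The administering nurses know the dose, but no role in recruitment is described for them. Emergency disclosure goes to the duty physician, concerns single patients, and is not to reach study personnel. To use the block structure, someone would have to collect successive patients' doses from several nurses and pass them on, against the protocol. If the separation holds, q = 0 and nothing can be deduced. This stands, and it is why one third is only a ceiling.

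Two further points also stand. A single dose does not always show the arm: under Modifications, both arms receive 40 mg in dialysis-free intervals with low creatinine clearance, and either arm may move to full treatment dosing after a thrombotic event. And the article does not say that blocks run within a centre. With a shared list, local staff would see only part of each block.

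It can also be said that small fixed blocks with opaque envelopes are a recognised design. That is true, but it does not rescue the stated reasoning. The article rests concealment on withholding the code, and that does not cover deduction from earlier doses. Here the block size is public and the dose is open to some staff on the recruiting units, so the protection depends on no information passing between colleagues.

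**Conclusion.** The point holds as an avoidable weakness in concealment. A single block size of four, published during recruitment, combined with unblinded administering nurses and a route of disclosure to duty physicians, would allow up to 33% of allocations (about 89 of 266) to be deduced with certainty. Reaching that figure needs every earlier allocation in the block and its starting point to be known. Under the assumptions shown, partial leakage gives about 8% (q = 0.5) or about 4% (one list, three equal centres, local doses only).

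A reader might infer that a third of allocations are predictable in this trial as it is run, or that recruiters have been selecting patients. The documents support neither. They describe blinded recruiters, knowledge of doses that nurses hold collectively and not individually, and no stated list per centre. Nothing in them shows that selection has taken place.

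**What to change.** For all envelopes not yet issued, and for any sites added later, have the pharmacy generate the remaining sequence with randomly varied block sizes such as 4, 6 and 8. Withhold the sizes from the sites and from public documents until recruitment ends. Replace the claim that hiding the code secures concealment with a description of this safeguard, and state whether lists are per centre. Splitting a shared list by centre would not help here, because local staff would then see more of each block. Adjusting the analysis for centre does not address predictability either.

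The cost is a new list from the pharmacy's existing system and a new set of envelopes. The statistical cost is slight imbalance if a block is left incomplete: at most 4 patients' difference per list with a block of 8, against 2 with a block of 4. On one list of 266 that is 135 against 131 at worst. The gain should be described modestly, because best-guess success falls only from about 71% to 68% for someone who knows the full history. Keeping doses from reaching recruiters therefore still matters.

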**Figure 1 F1:**
[figure not shown]
**Time schedule of enrolment, interventions, and assessments for participants.** Routine tests (APTT, platelets, D-dimer, AT, leukocytes, CRP, PCT, hematocrit), anti-Xa, and urine and plasma NGAL and Cr are measured at baseline. Following randomization, the patient will receive sc enoxaparin according to group allocation. Bedside clinical assessment for VTE and bleeding using validated scoring systems (Well's scores, HEME tool) will be conducted, and samples for hematocrit and platelet count will be taken daily. Bilateral lower extremity CUS will be conducted on the 1st, 3rd and 7th day of inclusion. Once weekly CUS (more frequent if DVT is suspected), as well as samples for peak anti-X_a_ (measured at 4 hours after enoxaparin dose) and trough anti-X_a_ (measured at 20 hours after enoxaparin dose) will be taken. Spiral pulmonary CT angiography and echocardiography will be performed on clinical suspicion of PE. During CRRT-free intervals with CrCl <30 ml/min/1.73 m^2^, group allocation will be discontinued and participants will receive 40 mg enoxaparin QD until the CrCl is >30 ml/min/1.73 m^2^ when enoxaparin dose according to group allocation will be resumed. Samples of urine and plasma will be taken for NGAL and Cr during CRRT-free intervals. APTT, Activated partial thromboplastin time; anti-Xa, Antifactor Xa; AT, Antithrombin; CRP, C-reactive protein; PCT, Procalcitonin; NGAL, Neutrophil gelatinase-associated lipocalin; Cr, Creatinine; sc, subcutaneous; VTE, Venous thromboembolism; CUS, Compression ultrasound; DVT, Deep venous thrombosis; CT, Computed tomography; PE, Pulmonary emboli; CRRT, Continuous renal replacement therapy; CrCl, Creatinine Clearance; QD, Once daily; HIT, Heparin-induced thrombocytopenia; ICU, Intensive care unit.

### Blinding

The medicine module of Critical Information System (CIS LIVE™; Daintel, Copenhagen, Denmark) used at all three hospitals allows for blinding. Patients, family members, clinicians, research personnel, radiologists, laboratory technicians, and the trial biostatistician will all be unaware of study-group assignments. They will remain blinded until the study database is locked at the end of the trial. Nurses who administer the drug will be the only party privy to the actual dose given to each patient as it is impossible to prepare an enoxaparin dose of 1 mg/kg beforehand. In the event of an emergency (major bleeding, need for major surgery), a participant’s allocated intervention may be revealed to the attending duty physician by the nurse providing care for that participant. The actual allocation will not be disclosed to the patient or study personnel, and there will be no disclosure of the code in any of the corresponding patient documents.

### Interventions

The intervention for the treatment arm will be 1 mg/kg enoxaparin sc QD, and the intervention for the control arm will be 40 mg enoxaparin sc QD. Enoxaparin will be administered to the thigh or abdomen of the study patients.

### Dispensing

Enoxaparin (Klexane™; Sanofi-Aventis Denmark A/S, Hørsholm, Denmark) 100 mg/ml is available as prefilled single-dose syringes containing 40 mg, or as multi-dose vials containing 300 mg in 3 ml. Nurses will carefully titrate a dose of 1 mg/kg, using 1 ml or 2 ml syringes as needed.

### Modifications

Project medicine will be adjusted in several situations. If creatinine-clearance (CrCl) is <30 ml/min/1.73 m^2^ during CRRT-free intervals, group allocation will be discontinued and participants will receive 40 mg QD. Once CrCl is >30 ml/min/1.73 m^2^, group allocation will be resumed. In the event of VTE, group allocation will be discontinued, and patients will receive a full treatment dose of enoxaparin. Enoxaparin will be temporarily discontinued in the case of oozing, and packed red blood cells, fresh frozen plasma, and protamine sulphate may be administered at the discretion of the attending physician. Enoxaparin will be resumed according to the group allocation when oozing is no longer observed. Should the platelet count decrease to less than 50 × 109/L, or if there is an unexplained platelet count decrease to less than 50% of baseline, or other suspicion of HIT, enoxaparin will be stopped and mechanical prophylaxis or the HIT-safe anticoagulant, argatroban(Novastan™; Swedish Orphan Biovitrum A/S, Lyngby, Denmark), will be started. The patient will be evaluated by the 4 T’s clinical scoring system [18] and blood samples will be taken for PF4/heparin enzyme-linked immunosorbent assay (ELISA) and 14C-platelet serotonin release assay.

### Adherence

To ensure protocol adherence and data quality, research coordinators attended study-specific training sessions. Throughout the trial participating centers will also educate rotating ICU residents and hold periodic updates for nurses. GCP monitoring will also serve to improve protocol adherence.

All the research physicians who will perform interventions on participants are trained in anaesthesia and intensive care, and as such have great experience with using ultrasound. In addition, all investigators received specific training in the performance of venous compression ultrasound (CUS) of the under extremities. The majority of these physicians also have prior training in Focused Assessed Transthoracic Echocardiography (FATE). All other aspects of care and management of trial outcomes are at the ICU team’s discretion.

### Adverse events

All serious adverse events will be immediately reported to the sponsor. The immediate reports will be followed within 24 hours by detailed written reports (please see Additional file 4). The investigator will also comply with the regulatory requirements related to the reporting of unexpected serious adverse drug reactions to the Danish national scientific ethical committee and the Danish Health and Medicines Authority.

The sponsor will expedite the reporting of all adverse drug reactions that are both serious and unexpected to all concerned investigators and/or institutions, the Danish national scientific ethical committee and the Danish Health and Medicines Authority within the timeframe specified by these authorities.

The sponsor will submit to the regulatory authorities all safety updates as required by these regulatory bodies. The following will not be reported: symptoms related to the patient’s underlying disease (such as fatigue, diarrhoea, pain, nausea, or vomiting), delirium, electrolyte imbalance, and death that ensues because of withdrawal of active treatment.

